### 2.9. Participant Timeline

The planned duration of the study is 24 months. Details about the data collection timeline are provided in Table 2. The last 6 months will be dedicated to manuscript writing, preparation of final reports, and dissemination of knowledge. Collaborative meetings will be held monthly throughout the entire study period.

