## Abstract

Prognostication of neurodevelopmental outcomes for neonates with hypoxic–ischemic encephalopathy (HIE) is primarily reliant on structural assessment using conventional brain magnetic resonance imaging in the clinical setting. Diffuse optical tomography (DOT) can provide complementary information on brain function at the bedside, further enhancing prognostic accuracy. The predictive accuracy and generalizability of DOT-based neuroimaging markers are unknown. This study aims to test the feasibility of prospectively recruiting and retaining neonates for 12 months in a larger study that investigates the prognostic utility of DOT-based biomarkers of HIE. The study will recruit 25 neonates with HIE over one year and follow them beyond NICU discharge at 6 and 12 months of age. Study subjects will undergo resting-state DOT measurement within 7 days of life for a 30–45-min period without sedation. A customized neonatal cap with 10 sources and eight detectors per side will be used to quantify cortical functional connectivity and to generate brain networks using MATLAB-based software (version 24.2). The Ages and Stages Questionnaires—3rd edition will be used for standardized developmental assessments at follow-up. This feasibility study will help refine the design and sample-size calculation for an adequately powered larger study that determines the clinical utility of DOT-based neuroimaging in perinatal brain injury.

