### 2.2. Study Setting

This study will be conducted at the McMaster Children’s Hospital neonatal intensive care unit (NICU). The province of Ontario, Canada’s perinatal services are organized into three levels, namely the following: (i) Level 1: low neonatal risk, postnatal care of healthy newborn and resuscitation/stabilization of ill infants before transfer; (ii) Level 2: neonatal care for gestational age > 32 weeks and birth weight > 1500 g [exception: Level 2c > 30 weeks and >1200 g]; and (iii) Level 3: neonatal intensive care for any gestational age and birth weight, availability of subspecialty consultants, and surgical capability. Since therapeutic hypothermia resources are available solely in Level 3 hospitals in Ontario, Canada, neonates born across Level 1 and 2 hospitals are transferred to Level 3 with a specialized neonatal transport team [www.pcmch.on.ca, 2 June 2025]. McMaster Children’s Hospital is a Level 3 unit attached to a high-risk maternal and fetal medicine unit. Approximately 50–60 neonates per year are admitted to the NICU with the diagnosis of HIE; ~90% of them receive therapeutic hypothermia, and ~80% of them are outborn neonates. Outborn neonates may be born in any of the surrounding Level 1 or Level 2 hospitals in the catchment area of McMaster Children’s Hospital. When indicated, passive cooling is started in the referring hospital, and the neonate is transferred immediately to the Level 3 unit to receive hypothermia therapy using a servo-controlled device. A two-member in-house neonatal transport team facilitates the transfer of neonates from the referring center to the Level 3 NICU.

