### 2.8. Objectives and Outcomes

#### Objectives and Corresponding Outcomes of the Feasibility Trial

Objective 1: To determine the feasibility of recruitment and retention strategies and data collection methods in the NICU. Feasibility will be assessed by reporting the following metrics: (i) The recruitment rate will be reported to assess the ability to recruit the target population within the desired timeframe, determined by the number of eligible participants who are enrolled in the study. We will maintain a recruitment tracking log. (ii) The follow-up rate will be used to assess the ability to retain participants and complete follow-up assessments, as determined by the percentage of enrolled patients who complete follow-up at 12 months. We will maintain a record of participant follow-up procedures and dropout rates. (iii) The rate of missing data will be determined by the percentage of completed data fields measured by reviewing collected data to identify any missing information, inconsistencies, or incomplete responses. *Criteria for Feasibility:* The main study will be feasible if the pilot study is successful based on the predefined criteria: (i) 80% of the eligible patients consent to the testing; (ii) 90% of the consented participants get DOT measurements taken before 7 days of life; (iii) for 80% of the consented participants, parent-reported developmental assessment is available at 6 and 12 months.

Objective 2: To assess the fidelity and safety of DOT measurements in neonates. (i) Safety will be assessed by reporting any adverse skin reactions to sensors or excessive agitation in the neonate, requiring early termination of the study. (ii) Data quality will be assessed by recording the degree of the signal-to-noise ratio. We will keep a record of the ability to properly place sensors with good contact and the ability to minimize motion artifacts and ambient light interference in each subject. (iii) Ability to complete adequate data acquisition within 45 min. *Criteria for Feasibility:* Time required for resting-state data acquisition per infant < 45 min.

Objective 3: To identify logistic challenges, unexpected adverse effects, or technical difficulties. Operational feasibility will be assessed based on the time and personnel required for each stage of the study, as well as the logistical challenges.

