Long-term neurological outcomes will be measured with a validated parent-reported questionnaire at 6 months and 12 months of age. We will use the Ages and Stages Questionnaire—3rd edition (ASQ-3) to assess five areas of childhood development—Communication, Gross Motor, Fine Motor, Problem-Solving, and Personal–Social—through parent/caregiver reports. Filling in the report takes 10–15 min, and it takes 2–3 min to score. The ASQ-3 is a widely used screening measure and has proven to be an effective developmental screening tool in cross-cultural populations [41]. The questionnaire includes 30 items, scored as yes, sometimes, or not yet, on questions about a child’s ability to perform a task [42]. The concurrent validity of the ASQ-3 with standardized testing of developmental (Bayley Scales of Infant Development) and intellectual (Stanford–Binet Intelligence Test–4th edition) skills has been demonstrated [43]. The ASQ-3 has a sensitivity of (0.70–0.90) and specificity of (0.76–0.91) in detecting developmental impairment, with retest reliability of (0.94–0.95) and interrater reliabilities between parents and professionals of (0.94–0.95) [44,45]. We will also use the Ages and Stages Questionnaire: socioemotional-2 (ASQ: SE-2) to perform a broadband social–emotional screening for study participants. Social–emotional domains include self-regulation, compliance, social communication, adaptive functioning, autonomy, affect, and interaction with people. ASQ: SE-2 test characteristics reflect an overall sensitivity of 81% across age intervals and an overall specificity of 84% across age intervals, with 89% test–retest reliability and 84% internal consistency [46]. Table 1 summarizes the study objectives, outcomes and corresponding data analysis. 

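### One year of recruitment, follow-up to 12 months of age and a 6-month write-up total 30 months in sequence, but the stated duration is 24 months

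*Protocol article*

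**What the plan says.** The durations appear in three places in the protocol article.

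- Section 2.9, Participant Timeline: "The planned duration of the study is 24 months", followed by "The last 6 months will be dedicated to manuscript writing, preparation of final reports, and dissemination of knowledge".
- Abstract: "The study will recruit 25 neonates with HIE over one year and follow them beyond NICU discharge at 6 and 12 months of age".
- Section 2.8, Objectives and Outcomes: "Long-term neurological outcomes will be measured with a validated parent-reported questionnaire at 6 months and 12 months of age". Table 2 shows the same two follow-up time points.

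Under Objective 1 of section 2.8, the follow-up rate is defined "as determined by the percentage of enrolled patients who complete follow-up at 12 months". Success criterion (iii), repeated in Table 1, is that "for 80% of the consented participants, parent-reported developmental assessment is available at 6 and 12 months". Section 2.10 makes sizing of the larger study conditional on the feasibility criteria being met. Table 1 lists a regression on the 6- and 12-month ASQ scores among the analyses meant to inform that sample size.

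**The concern.** Recruitment and follow-up between them need every one of the 24 months, while section 2.9 sets aside the last 6 for writing and final reports. That leaves 18 months for work that takes 24. All the durations are printed in the article, so this is a conflict between stated figures and not a detail left to a fuller document.

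It matters because completion at 12 months of age is the retention measure, a primary feasibility outcome, and criterion (iii) is part of the decision on whether the main study goes ahead. If the timetable in section 2.9 were followed literally, the final report would be in preparation while many infants were still too young for the assessment that defines the criterion. The 12-month scores intended to help size the definitive study would be incomplete for the same reason.

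**Working it through.** **Inputs**
- Total duration T = 24 months; write-up W = 6 months at the end (section 2.9).
- Recruitment R = 12 months; N = 25 infants (abstract).
- Follow-up F = 12 months of age (abstract, section 2.8, Table 2). Enrolment is in the first days of life, so this is about 12 months after entry.
- Threshold for criterion (iii): 80% of consented participants, which is 0.80 × 25 = 20 infants.
- Site volume 50–60 HIE admissions a year (section 2.2); consent target 80% of eligible patients (section 2.8).

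**Does the stated total reproduce?**
- In sequence: R + F + W = 12 + 12 + 6 = 30 months, against 24 stated. It does not.
- With write-up fully overlapping follow-up: R + F = 12 + 12 = 24 months. This fits, but the last infant reaches the 12-month ASQ at month 24, leaving no time for late questionnaires, final analysis or reporting.

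**Who is due when write-up begins?**
- Write-up begins at T − W = 24 − 6 = 18 months.
- Latest entry that gives 12 months of follow-up by then: 18 − 12 = month 6.
- Share due for the 12-month ASQ, assuming even accrual from month 0: 6/12 = 50%, or 12.5 of 25. With infants evenly spaced, the count is 12 or 13 depending on where the first is placed.
- Share due for the 6-month ASQ: latest entry is 18 − 6 = month 12, so all 25 are due.

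**Sensitivity of the 50%**
- Start-up delay of s months: share = (6 − s)/12, which is 42%, 33% and 25% for s = 1, 2 and 3.
- Random accrual at a constant rate: the number entering in the first half-year is binomial (25, 0.5), with a 95% range of 8 to 17 infants (32% to 68%). The probability that at least 20 have entered by month 6 is about 0.002.

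**Would faster accrual solve it?**
- Yield in 6 months at 80% consent, treating every admission as eligible: (50/2) × 0.8 = 20 to (60/2) × 0.8 = 24 infants.
- Time to reach 25: 25/(60 × 0.8) × 12 = 6.25 months to 25/(50 × 0.8) × 12 = 7.5 months.
- Section 2.6 sets gestational age and birth weight limits, and further exclusions are in Figure 1, which is not shown. The eligible number is therefore unknown, and 20 to 24 is an upper bound at that consent rate.

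**The case against.** The best defence is that section 2.9 does not say data collection or follow-up ends at month 18. The final assessments are short parent questionnaires, and authors can draft a manuscript while the last of them come in. On that reading the plan fits 24 months. The one-year recruitment period also appears only in the abstract; section 2.10 gives none.

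Part of this stands. Three stronger conclusions that a reader might draw are not supported:

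- *That criterion (iii) must fail for calendar reasons.* This would require the criterion to be judged at month 18, and the article sets no such cut-off.
- *That about 52% (13 of 25) is the most that could be achieved at month 18.* It is roughly the expected share under even accrual. If accrual ran at the upper-bound rate of 20 to 24 infants in 6 months, 80% to 96% of 25 would be due by then.
- *That the denominator would shrink to early enrollees.* Section 2.8 and Table 1 fix it as consented participants, and nothing suggests otherwise.

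The defence does not remove the conflict. Overlap is nowhere stated, and it sits badly with a period dedicated to writing that includes preparing final reports. Even with full overlap, the last assessment falls due at the end of the study. Faster recruitment contradicts the abstract and, on the site's own figures, would not clearly deliver 25 infants in 6 months.

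**Conclusion.** The point holds as a conflict between stated durations. The 24-month total is 6 months short of the sequential 30 and accommodates the stated recruitment and follow-up only if the write-up period is not kept separate. This arithmetic rests only on the printed figures and on entry in the first days of life.

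The consequence for criterion (iii) is conditional. Only if final reports used data available at month 18, with even accrual and no start-up delay, would about half the cohort have reached the 12-month assessment, against a threshold of 80%. No outcome, denominator or threshold in the plan is itself wrong. The correction is worth making because it protects a primary go/no-go criterion at little cost.

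**What to change.** Reconcile the abstract and section 2.9 in one of three ways:

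1. Restate the duration as about 30 months: 12 recruitment, 12 follow-up, 6 reporting.
2. Keep 24 months with a separate write-up by shortening recruitment to 6 months, and set an enrolment target that this period can deliver. On the article's figures that is at most 20 to 24 infants at 80% consent, and fewer if some admissions are ineligible.
3. State that write-up begins during follow-up, and that final analysis and reporting come after the last 12-month ASQ. With a full year of recruitment, this puts the final report beyond month 24.

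In each case, add a sentence saying that retention and criterion (iii) are evaluated on all consented infants, and only after the last enrolled infant's 12-month ASQ is due.

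The cost is a wording change and, under options 1 and 3, a longer administrative timeline. Option 2 may mean a smaller cohort. None of the three changes what participants are asked to do.

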### 2.10. Sample Size and Recruitment

The National Center for Complementary and Integrative Health notes that sample size should be based on practical considerations, including participant flow, budgetary constraints, and the number of participants needed to reasonably evaluate feasibility goals [47]. Hence, for this work, a sample size of 25 was considered adequate to reach saturation and establish feasibility. If the feasibility criteria are met, the sample size for the larger trial will be determined based on the data analysis.

### 2.11. Clinical Data Collection

Relevant clinical data collected per study subject will include the following: (i) Maternal demographics: maternal age, pregnancy complications, multiparity, smoking, medication, alcohol, drug abuse, mental illness, maternal infections, and education level. (ii) Intrapartum variables: mode of delivery, duration of the second stage of labour, risk factor for sepsis, Apgar scores, details of resuscitation, inborn/outborn. The following details will be collected about the NICU course and complications: (i) hypothermia therapy: time of initiation, time to reach the target temperature; (ii) severity of encephalopathy: modified Sarnat Staging; (iii) severity of end-organ dysfunction: MODS scoring system; (iv) seizures, anti-epileptic drugs; (v) length of stay, No. of days on a ventilator; (vi) need for assisted feeding (NG/G-tube), home oxygen, tracheostomy; (vii) neurophysiology: background pattern of amplitude-integrated EEG at 6 h, 24 h, 48 h, and 72 h.

## 3. Data Processing

We will follow a standard data-processing pipeline to analyze the collected fNIRS data. First, the raw data will be exported from OxySoft in the Shared Near-Infrared File (SNIRF) format, which retains optode positions and timestamps. Subsequently, the open-source NIRS data analysis software HOMER3, version 1.80.2 [48], will be employed to perform a series of preprocessing steps, including converting raw intensity data to hemoglobin concentration changes based on the modified Beer–Lambert Law [48]. The data preprocessing pipeline consists of the following steps:(1)Converting raw light intensity data to optical density change data;(2)Excluding channels with out-of-range signals or large standard deviations;(3)Correcting motion artifacts using Temporal Derivative Distribution Repair (TDDR), a regression-based approach that addresses motion-induced spikes and baseline drift [49];(4)Band-pass filtering (0.01–0.05 Hz) to eliminate low-frequency noise (e.g., data drift) and high-frequency physiological noise (e.g., cardiac signals);(5)Converting the preprocessed optical density data to hemoglobin concentration change data using a Differential Path Length Factor (DPF) of 6 for both oxy- and deoxyhemoglobin.

After preprocessing, resting-state functional connectivity and network analyses will be conducted using NIRS_KIT [50] and the Graph Theoretical Network Analysis Toolbox (GRETNA) [51], both of which are MATLAB-based open-sourced toolboxes. Pearson correlation coefficients will be calculated between all pairs of channels and among channels within specific ROIs. GRETNA will then analyze these correlation coefficients to characterize the topology of both whole-brain and ROI-specific networks. To investigate disruptions in specific neural networks, we will focus on the functional connectivity of the default mode, sensorimotor, auditory, and visual networks. These networks will be identified by co-registering the fNIRS recording channels to the standard MNI space using STORM-Net [52], a Python-based photogrammetry application (Version 3.13). We will then calculate global network metrics including **assortativity** (the tendency of nodes to connect with other nodes of similar degree), **hierarchy** (the degree of hierarchical organization), **small-worldness** (the ratio between local clustering and global integration), **global efficiency** (the efficiency of parallel information transfer), **local efficiency** (the network’s fault tolerance), and **synchronization** (the degree of correlated activity among nodes) [53]. These metrics provide insights into communication efficiency, information processing speed, network resilience, and overall connectivity. We hypothesize that hypoxic–ischemic injury will alter these network metrics, specifically manifesting as weaker interhemispheric connectivity and stronger intrahemispheric connectivity, which may represent compensatory adaptations during recovery.

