#### 2.7.2. Experimental Setup

We made the customized neonatal cap stitched in 3 sizes to snugly fit head circumferences of 33 cm, 35 cm, and 38 cm (Figure 3). The cap could be slightly stretched in all directions, allowing us to accommodate multiple head sizes and shapes without affecting the channels’ positions that correspond to the anatomical landmarks of the brain. We determined the optode positions based on the 10–20 international EEG system [35] for electrode placement. Each transmitter–receiver pair had a 2 cm distance between them as specified by the device (Figure 4). The cap had 20 emitters and 16 detectors, with 27 channels per side covering the frontal, parietal, and occipital lobes (Figure 4).

We will first set up the cap by placing the transmitter and receiver optodes into the optode holders based on the cap layout. We will start recording to take measurements during natural sleep. All infants will be breathing spontaneously in room air. No sedation will be given to the infant. Parents will be encouraged to be at the bedside, and the infant will be cuddled in a warm blanket before being placed in the cot. All recordings will be taken within two hours after feeding in a dimly lit room in the NICU. The total duration of the resting-state data acquisition will range from 30 to 45 min, depending on the infant’s cooperativeness.

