#### 2.7.3. Data Acquisition

Before initiating data acquisition, the fNIRS recording device will be prepared by establishing a high-fidelity wireless connection with OxySoft software (OxySoft 4) and ensuring the device is ready for measurement. The recording device and the computer will be placed on a hospital cart and brought into the NICU. The cart is positioned adjacent to the crib, and the fNIRS device will be set beside the patient (Figure 2b). Next, the NIRS cap will be placed on the patient’s head and adjusted so that the central optodes align with the nasion and all optodes are positioned perpendicularly to the scalp with adequate contact. Once the cap is secured, an automatic signal calibration will be performed. A brief video of the patient wearing the cap will be recorded to co-register the recording channels with brain regions.

OxySoft is proprietary software specifically designed for facilitating the collection, storage, visualization, and analysis of fNIRS data. It supports the parallel recording of multiple devices, enabling synchronized data acquisition from multiple fNIRS units. In this study, OxySoft version 4.0 will record, manage, export, and monitor data in real time during measurements. OxySoft provides data acquisition (DAQ) status and DAQ values during signal calibration and data collection, conveying information such as device status, recording time, total recording duration, and the amount of light detected in each fNIRS recording channel. Channels whose light levels exceed or fall below acceptable thresholds are highlighted in red. Such out-of-range values may arise from head movements that displace the cap, environmental noise, or the presence of hair between the optode and the skin. If this occurs during signal calibration, the cap will be readjusted to optimize optode–scalp contact and calibration will be repeated until the light levels fall within the acceptable range. The research team will continuously monitor the DAQ values throughout the study.

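### Channels are excluded and graph metrics are then computed on whatever remains, so size-sensitive network metrics may partly reflect signal loss

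*Protocol article*

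**What the plan says.** Section 2.7.2 gives the full array: "The cap had 20 emitters and 16 detectors, with 27 channels per side", which makes 54 channels. Section 2.7.3 explains why a channel's light level may be unacceptable: "Such out-of-range values may arise from head movements that displace the cap, environmental noise, or the presence of hair" under the optode. The remedy it describes applies to set-up: "If this occurs during signal calibration, the cap will be readjusted to optimize optode–scalp contact" and calibration is repeated. Once recording is under way, it says only that the values are monitored.

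Section 3 then lists five preprocessing steps. Step (2) is "Excluding channels with out-of-range signals or large standard deviations". Steps (3) to (5) are motion correction, filtering and conversion to haemoglobin change; none of them replaces or interpolates an excluded channel. After preprocessing, "Pearson correlation coefficients will be calculated between all pairs of channels and among channels within specific ROIs". GRETNA uses these coefficients to "characterize the topology of both whole-brain and ROI-specific networks". The section continues "We will then calculate global network metrics including" and names six: assortativity, hierarchy, small-worldness, global efficiency, local efficiency and synchronization.

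The secondary aims in Table 1 compare brain metrics by sex and by severity of encephalopathy with a t-test. They also relate brain metrics by regression to the MRI injury score and to ASQ scores. The regressions are meant to yield the sample size of the definitive study.

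**The concern.** In this sequence the channels are the nodes of the graph, so an excluded channel is a missing node. Movement, hair and ambient noise differ between infants and recordings, so the number and position of missing nodes will probably differ too. The order of the steps adds to this: exclusion for a large standard deviation comes before motion correction, so a channel disturbed by movement can be dropped before the correction that might have rescued it.

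Several graph metrics depend on how many nodes there are and where they lie. Two infants with the same connectivity could then have different efficiency values because one lost more channels. Two consequences follow:

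- **Added variance.** Variation in channel loss enters the metrics whether or not it differs by group. It therefore enters the estimates meant to size the larger study.
- **Bias.** If channel loss is related to sex or severity, the Table 1 comparisons can show a difference in network metrics where connectivity does not differ.

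**Working it through.** The article states no figure on this point, so there is nothing to reproduce. The check is how far channel loss alone moves the metrics.

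**Inputs from the article.** There are 27 channels on each of 2 sides, so 54 nodes (section 2.7.2). Recording lasts 30 to 45 min (2.7.2). The filter is 0.01–0.05 Hz, a bandwidth of 0.04 Hz (section 3). Planned enrolment is 25 (2.10).

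**Assumed, because the article does not give them.** The correlation structure, the thresholding rule, and the number and pattern of lost channels.

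**Channel pairs.** n(n − 1)/2 gives 54 × 53/2 = 1431 for the full array and 44 × 43/2 = 946 after losing 10. So losing 10/54 = 19% of channels removes 1 − 946/1431 = 34% of pairs.

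**Effective samples per recording.** 2 × bandwidth × time = 2 × 0.04 × 1800 = 144 for 30 min and 2 × 0.04 × 2700 = 216 for 45 min. The simulations used about 180.

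**Simulation A.** 60 infants with one common true structure (correlation decaying with distance, plus correlation between homologous sites), random removal and binary graphs.

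| Rule | Metric | 54 channels | 45 | 36 | SD at 54 | Shift in SD (45; 36) |
|---|---|---|---|---|---|---|
| 20% density | global efficiency | 0.530 | 0.523 | 0.512 | 0.006 | −1.2; −3.0 |
| 20% density | local efficiency | 0.684 | 0.675 | 0.655 | 0.015 | −0.6; −1.9 |
| r ≥ 0.3 | global efficiency | 0.602 | 0.598 | 0.587 | 0.033 | −0.1; −0.45 |

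For example, (0.523 − 0.530)/0.006 = −1.2 and (0.587 − 0.602)/0.033 = −0.45.

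**Simulation B.** A separately programmed check, again with identical true connectivity, with channels lost at random or as a contiguous patch. Synchronizability stands in for the plan's synchronization. Shifts are in SD from the full network, for 10, 15 and 20 channels lost.

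| Loss and rule | Global efficiency | Local efficiency | Synchronizability |
|---|---|---|---|
| random, 20% density | −0.8, −1.7, −2.7 | −1.0, −1.2, −1.6 | −0.3, −1.2, −1.9 |
| random, r > 0.35 | −0.4, −0.8, −1.3 | −0.9, −1.4, −1.7 | −1.0, −1.5, −1.9 |
| patch, 20% density | −2.4, −4.1, −5.0 | +0.4, +0.3, −0.1 | −2.1, −2.8, −3.1 |
| patch, r > 0.35 | +0.2, 0.0, +0.7 | +0.4, +0.1, +0.4 | −1.0, −1.3, −1.0 |

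Assortativity stayed within about 0.5 SD with no trend. Small-worldness moved little under random loss and by up to about 1 SD under patch loss. Hierarchy was not simulated.

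**Consequence if loss differs by group.** With 13 against 12 infants, no true difference, 2–6 channels lost in one group and 8–16 in the other, a nominal 5% t-test rejected as follows (300 replicates, so within about 3 to 6 percentage points):

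| Rule | Global efficiency | Local efficiency | Synchronizability | Assortativity |
|---|---|---|---|---|
| 20% density | 52% | 21% | 30% | 7% |
| r > 0.35 | 8% | 18% | 28% | 5% |

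Because all simulated infants share one true structure, the SDs above hold sampling noise only. Real infants differ in connectivity, which would make the standardised shifts and the rejection rates smaller.

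**The case against.** The strongest reply is that the article does not say channels are excluded separately in each infant, and that a node rule, a graph density and a minimum channel count are details an article may leave to a fuller document. The first part is literally true: exclusion by infant is an inference from the recording-specific causes in section 2.7.3, though a strong one. The second part would dispose of a complaint about a missing cut-off. It does not dispose of this point, because the article sets out the sequence itself, and exclusion followed by all-pairs graph metrics produces unequal networks. A fuller document could still contain a harmonising step.

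The article also limits channel loss. Calibration is repeated, recordings are made during natural sleep in dim light, motion is corrected, and contact and signal quality are recorded for each infant. This lowers the likely amount of loss but does not make the node sets equal.

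A reader might infer that the planned group comparisons are biased by 1 to 3 SD, or are likely to be falsely significant. The documents do not support that. Those figures need a 20% density rule, substantial loss and a denominator of sampling noise alone; with a fixed threshold the corresponding shift in Simulation A is 0.1 to 0.45 SD. Nothing in the article shows that loss differs by sex or severity. Nor can it be said that all six metrics are affected.

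The stakes are also limited. The aims concerned are exploratory, section 4 already warns that the small sample may mislead about associations, and Table 1 speaks of regional brain metrics without saying which ones will be tested.

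**Conclusion.** The point holds in a limited form. As written, the pipeline probably yields networks that differ in size and composition between infants, and some metrics then partly reflect signal loss. Synchronization was sensitive under both thresholding rules and both loss patterns. Global efficiency was sensitive under random loss and, at fixed density, under patch loss. Local efficiency was sensitive under random loss. Assortativity was not materially affected, and small-worldness moved only under clustered loss.

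The firm consequence is added variance in the estimates used to plan the larger study. Bias in the sex and severity comparisons is conditional on loss that differs by group. The magnitude cannot be fixed from the article: for 10 channels lost at random, global efficiency moved by 0.4 to 0.8 sampling SD depending on the thresholding rule, and less once real variation between infants is counted. The primary feasibility, fidelity and safety objectives are unaffected. The change is worth making because it is cheap and best settled before network results are seen.

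**What to change.** For the network analysis:

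1. Average the retained channels within predefined regions and use these regions as nodes, so that every infant has the same nodes. Where a regional network is to be analysed, its nodes must be smaller than the network.
2. Set a minimum number of retained channels per region and per infant for entry to the network analysis.
3. Compute the metrics at a common density. This helps only together with equal nodes: with unequal nodes, fixed density gave the larger shifts in global efficiency.
4. Report retained channels per infant and by group.
5. Repeat the Table 1 comparisons and regressions adjusted for the retained-channel count, as a sensitivity analysis.

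Keeping only channels retained in every infant is not a workable alternative. If each infant keeps 45 of 54 channels at random, the expected common set across 25 infants is 54 × (45/54)^25 ≈ 0.6 channels. At 5% random loss it is 54 × 0.95^25 ≈ 15.

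The cost is a few sentences of analysis text and some programming, with no new data and no change to the recordings. The drawbacks are coarser nodes, some infants possibly left out of the network analysis, and region averages that are noisier where fewer channels survive. The adjusted analysis is meant to show whether that last effect matters.
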